### Study population and participant recruitment

The study population will consist of persons belonging to the four high-risk groups as defined by the World Health Organization (WHO), except for healthcare workers: children six months to eight years, pregnant women, elderly ≥ 60 years, and adults with chronic diseases [7]. We have excluded healthcare workers from our targeted study population to prevent duplication with our prior research efforts [19]. We will enroll study participants who meet specific inclusion and exclusion criteria. Table 3 depicts the criteria utilized to determine the inclusion and exclusion of participants in our study.

**Table 3 Tab3:** List inclusion and exclusion criteria

Inclusion criteria	Exclusion criteria
Participants will be visiting study hospitals (outpatients and inpatients only. Not emergency departments) for routine care during the study period.	Participants with severe, life-threatening allergies to any ingredient in a flu vaccine (other than egg proteins)
Participants who will be children six months to eight years, or aged more than 60 years, or pregnant women (any trimester), or have any chronic disease such as chronic respiratory disease (requiring regular medication), diabetes, chronic renal disease, any cancer, excluding basal and squamous skin cancers, immune suppression or immune deficiency, chronic liver disease, chronic hematological disorder, chronic kidney disease, chronic neurological impairment/disease, serious mental health condition, organ or bone marrow recipient, history of any prior surgery, percutaneous coronary intervention, high blood cholesterol, family history of cardiovascular disease, other pre-existing conditions.	Participants having a history of severe allergic reactions (e.g., anaphylaxis) after a previous dose of influenza vaccine or to a vaccine component.
Participants /parents/caregivers who will be willing to sign the informed consent form	Participants having a history of Guillain-Barre syndrome less than six weeks after a previous dose of influenza vaccine.
Participants/parents/caregivers who will have an operational mobile phone number and are responsible for sharing updated phone numbers in case of plans to change for the next year	Participants having a history of moderate or severe acute illness with or without fever. The vaccine should be given after the acute condition has improved.

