#### Cost-effectiveness estimation

To estimate the cost-effectiveness of our pilot influenza vaccination porgramme targeted for the high-risk group, we will use the built-in formulas of the CETSIV tool. The CETSIV is a Microsoft Excel-based tool designed to analyze the cost-effectiveness of influenza vaccination using a decision tree model [43]. It features built-in formulas for deterministic Markov decision-analytic models to evaluate the incremental costs and DALY of the vaccination compared to a controlled scenario [43]. Besides, we will recheck the outputs by developing a deterministic Markov decision-analytic model to simulate outcomes under alternative assumptions of input parameters. Individual DALYs will be calculated for each risk group’s individual using the WHO global health estimates for DALYs [49]. Incremental cost-effectiveness ratios (ICERs) will be calculated as the ratio of incremental cost over incremental DALYs. We will conduct a probabilistic sensitivity analysis (PSA) to see how parameter estimation precision uncertainty affects the model’s outcome. Since we will develop a cohort-based Markov model, each model had different years of estimation depending on the age at which each cohort enters the mode. Hence, such calculated ICERs will be measured using different future time frames. In order to ensure consistency of ICERs across all cohorts, the discount will be applied to ICERs using the number of years remaining life years. We will assume a life expectancy of 75 and a discount rate of 5%. Identified key parameters will change simultaneously over predetermined probability distribution. The Markov model will be run 1,000 times for each risk group, assuming variations in key parameters using pre-defined probabilities to allow for uncertainty in parameters. If ICER is below less than three times the gross domestic product (GDP) per capita, we will consider the vaccination as cost-effective, as per the WHO standard [73–76]. Also, we will estimate rates of influenza cases averted /outpatient visits averted/hospitalization averted/ deaths averted, or influenza treatment cost or productivity loss averted by influenza vaccination in each risk group using the method described by Meredith et al. 2019 [77].

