### Vaccination cost estimation

We will be using the Flutool Plus add-on for Excel. Flutool Plus calculates each cost type’s financial and economic costs and displays the results. Besides Flutool Plus calculation, we will also calculate each cost type’s financial and economic costs for cross-checking purposes. To do so, we will multiply the data input quantities by the financial and economic unit costs to get the incremental financial and economic costs. However, the Flutool Plus tool’s default adjustment parameters, including the dollar exchange rate and inflation rate, were developed in 2021. We assume a discount rate of 5%. Bangladesh Bank’s dollars exchange rate of Tk.105 to Tk.110 will be used to represent the findings at all estimates [80]. According to the Bangladesh Bank, the inflation rate will also be adjusted with all of our estimates [81]. We will follow the process for four high-risk groups.

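### The plan discounts the finished ICER over remaining life years instead of discounting costs and DALYs before division; read literally, this lowers the child ICER 26- to 38-fold

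*Protocol article*

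**What the plan says.** All of the relevant text is in the protocol article under Cost-effectiveness estimation, unless another section is named.

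- The ratio is defined first: "Incremental cost-effectiveness ratios (ICERs) will be calculated as the ratio of incremental cost over incremental DALYs".
- The reason for a further step is that, in the cohort-based Markov model, "each model had different years of estimation depending on the age at which each cohort enters" the model, so the ICERs refer to different time frames.
- The remedy, offered for the sake of consistency across cohorts, is that "the discount will be applied to ICERs using the number of years remaining life years".
- The inputs follow: "We will assume a life expectancy of 75 and a discount rate of 5" per cent.
- The decision rule is applied to the ICER: "If ICER is below less than three times the gross domestic product (GDP) per capita", vaccination is called cost-effective.

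The section does not say that costs or DALYs are discounted before they are divided. The only other discount rate is under Vaccination cost estimation ("We assume a discount rate of 5" per cent), and it concerns programme costs alone. The groups, under Study population and participant recruitment, are "children six months to eight years, pregnant women, elderly ≥ 60 years, and adults with chronic diseases".

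**The concern.** A discount factor converts a cost or health effect in a given future year to its present value. A ratio of two totals has no year of accrual, so there is nothing in it to discount.

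The direction matters as well. Vaccine and delivery costs fall at the start. Life years saved by averted deaths accrue over decades. Discounting the two streams properly shrinks the denominator more than the numerator, so the ICER rises. If the averted DALYs all fall in the year of vaccination, it stays where it is. Multiplying the finished ICER by a factor below 1 moves it the other way.

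The exponent is the number of remaining life years, so the factor is smallest for the youngest cohort. The results for children, pregnant women, chronically ill adults and the elderly would each be rescaled by a different, purely age-driven amount before being held against one threshold. That defeats the stated purpose of the step and could change both a group's verdict and the order of the groups.

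**Working it through.** The article gives no ICER and no discount factor, so there is no figure of its own to reproduce. It gives no equation either; the formula in step 1 is the literal reading of its sentence.

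**Inputs.** Rate r = 0.05 and life expectancy 75 (Cost-effectiveness estimation). Ages 0.5 to 8 years for children and 60 as the lower limit for the elderly (Study population and participant recruitment). Remaining years L = 75 − age.

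**Step 1: the rule taken literally.** Multiplier on the ICER = 1.05^-L.

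| Age | L | Multiplier | Effect on ICER |
|---|---|---|---|
| 6 months | 74.5 | 0.0264 | 37.9-fold lower |
| 5 years | 70 | 0.0329 | 30.4-fold lower |
| 8 years | 67 | 0.0380 | 26.3-fold lower |
| 60 years | 15 | 0.481 | 2.1-fold lower |
| 75 years | 0 | 1.00 | none |
| 80 years | −5 | 1.28 | raised |

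For the other two groups the entry age is not given. As illustrations, the multiplier is 0.087 at 25 years (11.5-fold lower) and 0.295 at 50 years (3.4-fold lower).

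**Step 2: effect on the threshold.** An ICER passes if ICER × 1.05^-L < 3 × GDP per capita, so the ICER before this step may be as large as 3 × 1.05^L. That is 3 × 26.3 ≈ 79 times GDP per capita at 8 years, 3 × 37.9 ≈ 114 times at 6 months, and 3 × 2.08 ≈ 6 times at 60.

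**Step 3: what discounting the streams would do.** Take programme cost at year 0 and suppose that all DALYs are years of life lost (YLL). Discounted life years are A = (1 − 1.05^-L)/0.05, and the undiscounted ICER is multiplied by L/A.

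- 6 months: A = 19.47; 74.5/19.47 = 3.83
- 5 years: A = 19.34; 70/19.34 = 3.62
- 8 years: A = 19.24; 67/19.24 = 3.48
- 60 years: A = 10.38; 15/10.38 = 1.45

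**Step 4: gap between the literal rule and the correctly discounted ICER.** Gap = 1.05^L × L/A, if nothing was discounted before division.

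- 6 months: 37.9 × 3.83 ≈ 145
- 5 years: 30.4 × 3.62 ≈ 110
- 8 years: 26.3 × 3.48 ≈ 92
- 60 years: 2.08 × 1.45 ≈ 3.0

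**Step 5: sensitivity to the YLL share.** The article does not give the share s of undiscounted DALYs that are YLL, so it is an assumption here. With the remainder in year 0, the correct multiplier is 1/(s·A/L + 1 − s). At age 5, A/L = 0.276:

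- s = 1: gap 110-fold
- s = 0.9: 1/0.349 = 2.87; gap 87-fold
- s = 0.5: 1/0.638 = 1.57; gap 48-fold
- s = 0: multiplier 1; gap 30-fold

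If the streams had already been discounted before division, the extra step on the ratio would alone leave the child ICER 26- to 38-fold too low, whatever the YLL share.

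**The case against.** **The sentence may be loose wording.** The authors may have meant discounting DALYs over the remaining-life horizon. That is possible, and the executed calculation cannot be seen. But the ratio is defined first and the discount is then placed on ICERs already calculated, and nothing else in the article supports the milder reading. If it is what was meant, the sentence still has to be rewritten.

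**The main estimate comes from CETSIV.** The section says that the tool's built-in formulas will be used and that the self-built Markov model rechecks them. The discount sentence follows from the mention of the cohort-based Markov model. This objection stands in part: the article does not show how CETSIV discounts, so the finding cannot be extended to its output. It does not excuse the rule for the model to which it applies. Two tools meant to check each other would also disagree for no substantive reason.

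**Stronger readings that do not hold.**

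- A reader might take an error of about 100-fold in children as established. It needs DALYs that are nearly all YLL and no discounting before division. Neither is stated, and under those assumptions the range is 92 to 145, so 100 is not an upper limit either.
- A reader might infer that deaths averted above age 75 count for nothing. The article takes DALYs from WHO estimates and nowhere says that YLL equal 75 minus age.
- A reader might conclude that the verdict reflects only the discount formula. A rescaled ICER still contains vaccine cost and effect.

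**Conclusion.** The rule is wrong as written and must be corrected. From the article's own rate, life expectancy and age limits, the literal step lowers the ICER 26- to 38-fold in children and about 2-fold at age 60. It acts in favour of a cost-effective verdict for every cohort entering below 75. It makes the groups less comparable, contrary to its stated aim.

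The distance to a correctly discounted child ICER is conditional: about 92- to 145-fold if all DALYs are YLL and nothing was discounted beforehand, and smaller with a lower YLL share.

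The fixed 75 is a secondary defect. The elderly group has no upper age limit, and for any cohort given an entry age above 75 the exponent turns negative and the discount inflates the ICER. No entry age for that cohort is stated, so whether this happens is open.

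The defect in the wording is certain. Its size in the final results depends on how the Markov model is coded.

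**What to change.** Delete the sentence that discounts the ICER. State instead that costs and DALYs will each be discounted at 5% per year to the year of vaccination, that the ICER is discounted incremental cost divided by discounted DALYs averted, and that no further discount is applied to the ratio. Apply this in the Markov model, confirm how CETSIV discounts, and report both on the same basis. Replace the fixed life expectancy of 75 with remaining life expectancy conditional on age, from a life table, so that the oldest cohorts keep positive remaining years. Different entry ages then need no separate adjustment, because every stream is brought to the same reference year.

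The cost is a short rewrite of the analysis text and a formula change in the Markov spreadsheet, with no extra data collection from participants. The downside is that ICERs, above all for children, will be less favourable than under the literal rule.

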Elderly ≥ 60 years influenza vaccine doses	One dose for all persons aged 60 years and older. Population data from the Statistical Yearbook of Bangladesh 2020 [26]. Monthly the total number of ≥ 60 years aged patients visited hospitals will be collected from respected hospitals or respective District Civil Surgeon Office [29, 30, 33].
Adults with chronic diseases, influenza vaccine doses	One dose for all persons with chronic disease. We will use the prevalence of having any chronic illness from the Bangladesh Household Income and Expenditure Survey (HIES) 2010 [35]. Then, the total number of persons with any chronic illness will be estimated using data from the Statistical Yearbook of Bangladesh 2020 [26]. Monthly patients with chronic diseases visited hospitals will be collected from respected hospitals or respective District Civil Surgeon Office [29, 30, 33].

We will conduct all the study activities through close collaboration with the Institute of Epidemiology Disease Control and Research (IEDCR) of the Ministry of Health and Family Welfare (MoH&FW), the Government of Bangladesh. We will also collaborate closely with the administration of the participating hospitals, especially the hospital director, to guarantee the hospitals’ participation, support, and cooperation. We will work with the line director and directors of study hospitals to implement the vaccination. We will utilize hospital resources and leverage existing staff to vaccinate study participants. Figure 1 illustrates the study activities and data collection flow chart.

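### The 5% discount is applied to the finished ICER over remaining life years, so the result depends on entry age and can reverse the cost-effectiveness verdict, above all for children

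*Protocol article*

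**What the plan says.** All the relevant steps are in the protocol article under Cost-effectiveness estimation, in this order.

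- The ratio is defined: "Incremental cost-effectiveness ratios (ICERs) will be calculated as the ratio of incremental cost over incremental DALYs".
- The cohort Markov model is said to have a horizon that varies by cohort: "each model had different years of estimation depending on the age at which each cohort enters the mode".
- From this the article concludes that "such calculated ICERs will be measured using different future time frames".
- To make the cohorts consistent, "the discount will be applied to ICERs using the number of years remaining life years".
- The inputs are given: "We will assume a life expectancy of 75 and a discount rate of 5" per cent.
- The decision rule follows: "If ICER is below less than three times the gross domestic product (GDP) per capita", vaccination is called cost-effective.

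The section does not say that yearly costs or DALYs are discounted before the ratio is formed, and it writes out no formula for the discount on the ICER. The section Vaccination cost estimation repeats the 5% rate, but only for programme costing.

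The groups to be compared are "children six months to eight years, pregnant women, elderly ≥ 60 years, and adults with chronic diseases" (Study population and participant recruitment). Table 1 sets no upper age limit for the elderly group: "One dose for all persons aged 60 years and older".

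**The concern.** Discounting converts an amount that falls in a future year to its value today. Costs and DALYs in each model year are such amounts. Their ratio is not, because it has no date. Applying a discount factor based on remaining life years to the ratio multiplies it by a number that depends only on the cohort's age at entry. The step is meant to make cohorts comparable, but it introduces an age-dependent difference between them. Streams that have each been discounted to the vaccination season would need no further correction for different horizons.

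The adjusted ratio is then judged against three times GDP per capita, which is not adjusted in the same way. A group with a young entry age therefore faces a much looser test than an older group. Cost-effectiveness by risk group is a main objective and is intended to inform national vaccination policy, so both the verdict for each group and the order of the groups are at stake.

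**Working it through.** The article states no discount factor, ICER or GDP value, so there is no figure of its own to reproduce. The check works out what the stated rule implies.

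**Inputs.** Discount rate 5% and life expectancy 75 (Cost-effectiveness estimation); limit of 3 × GDP per capita (same section); children from six months to eight years and elderly from 60 with no upper limit (Study population; Table 1). Ages 4, 25, 45 and 65 are illustrative, because the article gives no entry ages for its cohorts.

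**Step 1: the rule on its plain reading.** Remaining years n = 75 − age, and adjusted ICER = ICER / 1.05^n.

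**Step 2: the largest unadjusted ICER that still passes.** ICER / 1.05^n < 3 × GDP, so ICER < 3 × 1.05^n × GDP.

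**Step 3: comparison with year-by-year discounting, scenario A.** Assume that all cost falls in the vaccination season and that the benefit is one life year in each remaining year. The n undiscounted years become a(n) = (1 − 1.05^−n)/0.05, so the ICER is multiplied by n / a(n). For age 4: a(71) = 19.37 and 71/19.37 = 3.66, rounded from unrounded values.

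| Entry age | n | ICER divided by 1.05^n | Largest ICER that passes (× GDP) | Scenario A: ICER multiplied by |
|---|---|---|---|---|
| 0.5 | 74.5 | 37.9 | 113.7 | 3.83 |
| 4 | 71 | 31.9 | 95.8 | 3.66 |
| 8 | 67 | 26.3 | 78.8 | 3.48 |
| 25 | 50 | 11.5 | 34.4 | 2.74 |
| 45 | 30 | 4.32 | 13.0 | 1.95 |
| 60 | 15 | 2.08 | 6.2 | 1.45 |
| 65 | 10 | 1.63 | 4.9 | 1.30 |
| 75 | 0 | 1.00 | 3.0 | – |
| 80 | −5 | 0.78 | 2.35 | – |

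**Step 4: scenario B.** If costs and DALYs averted have the same yearly profile, so that cost in year t is k times DALYs averted in year t, both discounted sums shrink by the same proportion. The ICER stays at k, and year-by-year discounting leaves it unchanged. The multiplier from correct discounting at age 4 therefore runs from 1 to about 3.7 across the two scenarios.

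**Step 5: distortion between groups.** The same unadjusted ICER would look 1.05^(71 − 10) = 1.05^61 = 19.6 times better at age 4 than at age 65.

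**Step 6: ages of 75 and over.** At 75 the exponent is zero and nothing changes. At 80 it is −5, so the rule divides by 0.78 and raises the ICER. The elderly group includes such participants.

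**The case against.** The strongest reply is that the formula is an inference. The article never writes ICER/1.05^(75 − age). Remaining life years and a rate are also the inputs to ordinary present-value discounting of life years, and a condensed article may loosely mean that ICERs are reported on a discounted basis. If so, only the wording is at fault. This stands as a limit on the magnitudes. It does not remove the point: the reason given is that ICERs already calculated need adjusting for consistency, and that describes a step taken after the ratio is formed.

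Second, the sentence belongs to the description of the cohort Markov model, which rechecks the output of the CETSIV tool. The article does not say which model's ICER is compared with the threshold, or how CETSIV discounts. This also stands. If CETSIV already discounts the yearly streams and the rule is then applied to its ICER, that result is discounted twice; if the rule covers only the recheck model, the two models may disagree for no substantive reason.

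Third, a reader might infer that the rule settles the verdict and that age alone sets the ranking of groups. The documents do not support this. They give no ICER and no GDP figure. The adjusted ratio still depends on effectiveness, illness cost and programme cost. An ICER already below 3 × GDP keeps its verdict at any entry age under 75, and a cost-saving result keeps its sign.

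Fourth, a reader might combine the division by 32 with the 3.66-fold increase and report an error of about 117-fold at age 4, or say that the rule always moves the ICER in the wrong direction. Both depend on scenario A. The article describes multi-year horizons, annual vaccination and productivity lost to deaths, and does not settle when costs fall relative to DALYs.

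**Conclusion.** The rule as written is wrong. It is a stated method, not a detail left out of a condensed article, and nothing elsewhere in the article repairs it. It makes the ICER a function of entry age and defeats its own aim of consistency between cohorts.

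On the plain reading it biases towards a finding of cost-effective at every entry age below 75. The verdict would be reversed for an unadjusted ICER between 3 and about 96 × GDP at age 4, 34 × at 25, 13 × at 45 and 4.9 × at 65. The scope for reversal is thus very wide for children and modest for the elderly, and the order of the risk groups can be distorted. These figures rest on the single-sum formula and on illustrative ages. Confidence is high that the rule is wrong and moderate as to its size. Whether any verdict would in fact change cannot be determined from the article.

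**What to change.** Replace the sentence with: *Costs and DALYs in each model year are discounted at 5% to the vaccination season; the ICER is the ratio of the two discounted sums; no further discount is applied to the ICER.*

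In addition:

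- apply this to both the CETSIV output and the recheck Markov model, and say which ICER is compared with the threshold;
- confirm that neither CETSIV nor the DALY inputs are already discounted, so that no discount is applied twice;
- state how cohorts aged 75 and over are handled under a life expectancy of 75;
- show results with undiscounted DALYs as a sensitivity analysis.

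The cost is one sentence and a spreadsheet change, with no new data. The downside for the sponsor is that ICERs may become less favourable than under the stated rule, mostly in the younger groups.
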